### Missing data

To contain the number of missing data and patient dropout, telephone contact with individuals who missed scheduled visits, or their caregivers, was planned offering the option of a remote visit if attendance was not feasible. No missing data will be accepted in the evaluation of biomarkers; therefore, it is required that all participants have a full evaluation of the biomarkers under study. A high level of completeness is expected for the main baseline characteristics, especially for age, sex and level of education. At least 80% of completeness will be required to include predictive factors in the analysis and the multiple imputation techniques by chained equations will be applied for dealing with missing data. Missing values for continuous normally distributed data will be imputed using linear regression, while the predictive mean matching method will be applied for not normally distributed data. Logistic regression will be used for binary data and ordinal logistic for ordered categorical data [43]. All predictors, including socio-demographic and clinical variables and biomarkers, will be considered potential variables for the imputation model. The outcome variable will be included in the imputation model adding the censoring indicator and the cumulative baseline hazard function estimated with the Nelson–Aalen method. For each variable with missing data to be imputed, candidate variables for inclusion in the imputation model will be selected based on their association with the missingness indicator. Associations will be assessed using *t*-test for continuous variables and chi-square test for categorical variables, with a *p*-value threshold of 0.05. If the frequency of missing data is less than 5% for each selected predictive variable, the main analysis will be conducted using only one imputed value generated according to the approach described above using the predictive mean imputation with 5 nearest neighbours to preserve variance and avoid the inflation of associations among the variable and predictors. A complete case analysis will be performed on this imputed dataset.

#### Internal validation

The final predictive model will be internally validated using the bootstrap technique with 500 bootstrap samples [38]. The stepwise selection will be repeated in the validation process (i.e. stepwise procedure will be repeated within each bootstrap sample). Consequently, Harrel’s c-index of the predictive model will be adjusted to take into account the estimated potential overfitting and a corrected c-index will be reported. Apparent and corrected calibration measures will be reported [44]. The correction will be performed using the shrinkage factor calculated with bootstrapping. The shrinkage factor may take values between 0 and 1, and a value above 0.90 indicates a small overfitting. As the shrinkage of regression coefficients is an important way to reduce overfitting, the shrinkage factor will be also applied to regression coefficients and intercept of the final model [38] to improve the prediction ability of the regression model when applied to external data. Both the original and shrunken regression coefficients will be reported.

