**CSF biomarkers**		
Aβ (1–42)	≤ 640 pg/ml	Bellomo et al. 2021 [28]
Total-tau	≥ 404 pg/ml	Bellomo et al. 2020 [29]
Phosphorylated Tau 181 (p-Tau)	≥ 56 pg/ml	Bellomo et al. 2020 [29]
Ratio Aβ_1-42/1–40_	≤ 0.068	Doecke et al. 2018 [30], Leitão et al. 2019 [31]
**Ratio** Aβ_1-42 /p-Tau_	≤ 11.8	Leitão et al. 2019 [31]
**EEG**	Classified in physiological vs pathological based on Small World for the seven EEG frequency bands using machine learning technique	Vecchio et al. 2023 [32]
**FDG-PET**	Classified in negative and positive (AD-like, other forms) using the optimised SPM procedure	Della Rosa et al. 2014 [10], Perani et al. 2014 [11]
**APOE- e4**	Classified in none, one allele, both the alleles	

However, these cut-offs were determined to discriminate between normal cognition and AD, but the population under study is at higher risk of developing dementia compared to the normal population. Therefore, for continuous biomarkers the receiver operating characteristic (ROC) curves will be used to identify new optimal cut-offs for the specific population under study. For biomarkers known to be influenced by sex and/or age, the corrected values will be used. In this context, sensitivity and specificity are both considered targets for determining the optimal cut-off; therefore, among all the commonly used methods [33], the distance to the left-upper corner was chosen. This method maximises both sensitivity and specificity and guarantees a better balance between the two measures [34]. Warnings are raised about its use as not always the method leads to an optimal cut-off in the intention of maximising overall correct classification rates compared to the commonly used Youden’s method [35]; therefore, Youden’s method will be also provided for comparison.

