#### Statistical model and variable selection

Initially, an analysis of socio-demographic and clinical variables will be conducted using the Cox model to identify a core of variables significantly associated with the outcome that will be included in the development of the prognostic multivariable model. A check of multicollinearity between predictors will be assessed, then a stepwise selection starting from the full model will be applied using a threshold of 0.10 for removal and 0.05 for re-admission of variables. A final check of variables not selected by stepwise will be conducted using the likelihood ratio test [36, 37]. Age and sex will be forced in the procedure selection and retained in the final model. Subsequently, these selected variables will be included in multivariable models with the addition of individual biomarkers one at a time. The additional predictive value of each biomarker beyond clinical and socio-demographic variables will be calculated. The performance results will be used to determine for each biomarker which form (continuous or categorical) will be chosen for the development of the multivariable prediction model. Categorisation is typically preferred for the application in clinical practice, but as any categorisation implies a loss of information, we will select the biomarker in a categorical form if the loss in performance could be considered negligible with respect to the continuous form. Categorisation will also be chosen in cases where non-linearity is detected for the continuous form. The categorisation according to the threshold provided by the experts (Table 3) will be preferred in case a small loss of performance is observed compared to the continuous form.

The final predictive model will be identified through a multivariable model considering as eligible predictors all the biomarkers and all selected predictors among the clinical and socio-demographic variables using the stepwise selection procedure as described above. Age and sex will be forced into the model selection process. A final check of the result from the automatic selection procedure will be conducted to ensure that no significant biomarkers were excluded and, vice versa, that no negligible biomarkers were included.

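### The bootstrap is specified to repeat only the stepwise procedure, so the corrected c-index and shrinkage factor lean modestly optimistic; shrinkage is also applied to an intercept that a Cox model does not have

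*SAP article*

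**What the plan says.** Under Internal validation, the SAP article validates the final model "using the bootstrap technique with 500 bootstrap samples" and states what is repeated: "The stepwise selection will be repeated in the validation process (i.e. stepwise procedure will be repeated within each bootstrap sample". From this come a corrected c-index, corrected calibration measures and a shrinkage factor. That factor is then used on the model itself: "the shrinkage factor will be also applied to regression coefficients and intercept of the final model".

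The model is built in several steps on the same data:

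- Statistical model and variable selection starts with a Cox analysis of the clinical variables to "identify a core of variables significantly associated with the outcome". This uses a stepwise procedure (0.10 for removal, 0.05 for re-admission) and a likelihood ratio check of the variables left out.
- Statistical analysis method says that for continuous biomarkers ROC "curves will be used to identify new optimal cut-offs for the specific population under study".
- The form of each biomarker is then settled on the data: "The performance results will be used to determine for each biomarker which form (continuous or categorical) will be chosen". A categorical form is taken if the loss is negligible or if non-linearity is found. The Table 3 cut-offs are preferred if the loss is small. Neither negligible nor small has a number.
- The final stepwise run takes all biomarkers plus the clinical variables already selected.
- Afterwards: "A final check of the result from the automatic selection procedure will be conducted to ensure that no significant biomarkers were excluded", and conversely that no negligible ones were kept.

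**The concern.** A bootstrap optimism correction estimates how much a model-building process flatters itself, but only for the parts of that process rerun in each sample. Choices made once on the full data and then carried fixed into every sample contribute optimism that the correction cannot see. Here the stated scope is narrower than the process it is meant to validate.

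This matters more than usual because the Discussion names the lack of external validation as a major limitation, so internal validation carries the evidence. The shrinkage factor also scales the coefficients behind the nomogram and the risk groups, which Model presentation and risk groups intends as support for treatment decisions.

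The second problem is the word intercept. The final model is Cox, and its partial likelihood contains none. The quantity with that role in a predicted 3-year risk is the baseline survival. The plan does not say what happens to it once the coefficients are shrunk.

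**Working it through.** **1. Steps set against the stated scope**

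| Step using the outcome | Section | Repeated in the bootstrap, as written? |
|---|---|---|
| Clinical core, by stepwise | Statistical model and variable selection | Unclear: it is a stepwise run, but the final run starts from an already selected set |
| ROC cut-offs | Statistical analysis method | Not stated |
| Continuous or categorical form | Statistical model and variable selection | Not stated; no numerical limit |
| Categorisation on non-linearity | Same, and Checking assumptions and variable handling | Not stated |
| Final stepwise run | Statistical model and variable selection | Yes |
| Closing check | Same | Not stated; no numerical rule |

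**2. The plan's nearest figure**

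The article gives no figure for optimism. The nearest is the shrinkage-based sample size. With R² = 0.31 (Sample size) and a target shrinkage S = 0.90 (assumed; not stated there):

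- n per parameter = 1/[(S − 1)·ln(1 − R²/S)] = 1/[(−0.10)·ln(1 − 0.31/0.90)] = 23.68
- event fraction = 0.16 × 2.5 = 0.40
- events per parameter = 23.68 × 0.40 = 9.47 (stated 9.5)
- 400 × 0.40 = 160 events, and 160/9.47 = 16.9 (stated 17)

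The figures reproduce.

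**3. Size of the optimism left over**

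Cox simulation with n = 400 and about 40% events. There were 15 clinical parameters, 11 continuous biomarkers (MMSE, DFR, five CSF measures, four hippocampal volumes) and 5 other biomarker parameters. Selection was backward at p = 0.10 with age and sex forced. Each design had 50-60 data sets with 25 bootstraps each, and truth was taken from new samples of 3000.

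Three bootstraps were compared: A repeats the final stepwise only; B repeats the clinical and final stepwise; C also repeats ROC cut-offs and form choice.

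| Design | c: true / A / B / C | Slope: true / shrinkage A / B / C |
|---|---|---|
| True c about 0.80; categorical form if loss ≤ 0.01 (assumed limit) | 0.805 / 0.818 / 0.814 / 0.810 | 0.816 / 0.855 / 0.834 / 0.823 |
| Same signal; best-performing form | 0.808 / 0.816 / 0.811 / 0.809 | 0.828 / 0.853 / 0.831 / 0.826 |
| Weaker signal; loss ≤ 0.01 | 0.716 / 0.736 / 0.729 / 0.723 | 0.756 / 0.836 / 0.803 / 0.785 |

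Differences, from unrounded means:

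- A − C: 0.008, 0.007, 0.013 in c; 0.032, 0.027, 0.051 in shrinkage.
- B − C: 0.004, 0.002, 0.005 in c; 0.011, 0.005, 0.018 in shrinkage.
- A − truth in c: 0.818 − 0.805 = 0.013; 0.816 − 0.808 = 0.008; 0.736 − 0.716 = 0.020.

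More than half of the A − C gap in c disappears once the clinical stepwise is repeated. In the first design, (0.0081 − 0.0039)/0.0081 = 52%.

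Monte Carlo standard errors are at most 0.003 for c and 0.010 for slopes; none was computed for the paired differences. Re-admission, categorisation on non-linearity, the likelihood ratio check and the closing check were not simulated.

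A separate logistic simulation (n = 400, true c 0.723) cut the biomarkers at the ROC point closest to the corner. Corrected c was 0.753 with stepwise-only repetition and 0.732 with full repetition, a gap of 0.021. The shrinkage factors were 0.81 and 0.73. The gap therefore grows if ROC-derived cuts dominate.

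**4. The intercept**

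Predictive performance mentions a calibration intercept, but that is a performance measure and not a term of the model. Model presentation and risk groups centres the covariates for the nomogram. Centring fixes the reference patient but supplies no intercept to shrink. A 3-year risk is 1 − S₀(3)^exp(linear predictor). When the coefficients shrink, S₀(3) has to be re-estimated to match, and the article does not say that it will be.

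**The case against.** Several replies have force.

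- *The clinical core.* Its selection is itself stepwise, and the final run reuses the same procedure, so the sentence in Internal validation can be read as covering both. A reader might infer that it is plainly left out; the text does not settle this. Since it drives more than half of the simulated gap in c, the smaller range has to be reported too.
- *The closing check.* A reader might call it a manual judgement that cannot be bootstrapped. The article says only that it looks for significant biomarkers excluded and negligible ones included. It is under-specified, but it could be coded.
- *Size.* A reader might take the logistic result, in which c stayed 0.753 − 0.723 = 0.030 above truth, as the expected bias. The plan does not support that: it uses Cox, expects c = 0.8, prefers Table 3 cut-offs when the loss is small, and needs no ROC search for EEG, FDG-PET or APOE.
- *The 0.90 benchmark.* Both approaches fall below it in every simulation, so the plan would report more than small overfitting and shrink the coefficients either way.
- *The intercept.* Multiplying the log cumulative baseline hazard by 0.85 would move a 30% risk to 1 − exp{−exp[0.85·ln(−ln 0.70)]} = 34.1% (by 0.80: 35.5%). A reader might infer that the nomogram will be off by this much, but no section says the factor would be used that way.
- *Other safeguards.* Sensitivity analysis adds other thresholds and LASSO, and the Discussion discloses the categorisation trade-off. These vary the selection; they do not correct optimism from cut-offs or form choice.

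These replies reduce the size and remove the stronger claims. The mismatch between what is built and what is validated remains, as does the wording error.

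**Conclusion.** The point stands in modest form and should be fixed before analysis. Followed as written, the bootstrap under-corrects. The direction was the same in all three Cox designs. Relative to full repetition, the excess is about 0.007-0.013 in c and 0.03-0.05 in the shrinkage factor if only the final stepwise is repeated. It is 0.002-0.005 and 0.005-0.018 if the clinical stepwise is covered as well. It is larger if most biomarkers enter with ROC-derived cuts.

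These sizes depend on an assumed correlation structure, an assumed 0.01 limit for negligible loss in two of the three designs, and 400 evaluated participants. The Discussion says the enrolment target was missed but gives no final number, and smaller samples were not simulated.

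The intercept is an error of specification whose numerical effect cannot be given, because the plan does not say what would be done with the baseline. What can be said is that the nomogram's 3-year risks depend on a quantity left unspecified after shrinkage.

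**What to change.** In Internal validation:

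1. State that every outcome-dependent step is rerun in each bootstrap sample: clinical-core selection, ROC cut-offs, form choice, categorisation on non-linearity, stepwise selection and the likelihood ratio check.
2. In Statistical model and variable selection, give numerical limits for negligible and small loss of performance so that form choice can be programmed.
3. Write the closing check as a coded rule and include it in the bootstrap, or drop it.
4. Replace the reference to the intercept: shrink the coefficients, re-estimate 3-year baseline survival with the shrunken linear predictor as an offset, and build the nomogram from that.

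The cost is programming and computing time, with no new data. The reported corrected c-index will probably be slightly lower.

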#### Sensitivity analysis

As sensitivity, the robustness of the stepwise procedure for the selection of variables in the final model will be performed by repeating the stepwise selection considering different levels of p for removal and for re-admission and using the Akaike information criterion (*p* ≤ 0.157). Additionally, the least absolute shrinkage and selection operator (LASSO) method will be used, and the tuning parameter lambda will be chosen by tenfold cross-validation. The predictive performance of the models will be compared.

A complete case analysis will be performed for the final model if the number of missing data will be contained.

Additionally, the competing risk analysis will be performed taking into account death as a competing event using Fine and Gray’s semiparametric proportional sub-distribution hazards model.

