#### Predictive performance

For each biomarker in the categorical form, the accuracy measures (sensitivity, specificity, positive predictive value, negative predictive value, overall accuracy, positive and negative likelihood ratios) will be calculated for comparison with the literature. For continuous biomarkers, the area under the receiver operating characteristic curve (AUC) will be also reported. Moreover, a univariate analysis will be conducted using the proportional hazard Cox model.

To evaluate the performance of the prediction models, several measures will be considered. The concordance c-index with its 95% CI will be provided as a discrimination measure and the extensions of binary AUC to survival analysis proposed by Harrell will be used [40, 41]. The Akaike information criterion will be provided as a measure of the goodness of fit of the model.

The added value on performance of each biomarker to the multivariable model with demographical and clinical variables will be assessed by the category-free Net Reclassification Improvement (NRI), which is the net proportion of events reclassified correctly plus the net proportion of non-events reclassified correctly. The delta AUC (difference in c-statistics) will be also provided [41], and the likelihood ratio test will be used to assess the statistical significance of the incremental contribution of each biomarker [36, 37].

In addition, to assess the predictive performance of the final multivariable model, calibration measures will also be reported [38, 42]. A calibration plot will be done by plotting the observed outcome proportion (on the *y*-axis) versus the ordered predicted outcome probabilities (on the *y*-axis) by quantile of the predicted risk. Subsequently, the calibration intercept and slope and their 95% CI will be estimated. There is a perfect calibration when the intercept is zero and the slope is one. Moreover, overall measures of performance, the Nagelkerke’s *R*^2^ and the Brier score, will be provided. The Brier score is a composite measure of discrimination and calibration with lower scores indicating improved model accuracy, and it will be calculated at a fixed time point (3 years).

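### Optimism correction covers only the final model's c-index, calibration and coefficients, leaving the Brier score and R² optimistic and the comparison of selection rules without a like-for-like corrected basis

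*SAP article*

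**What the plan says.** In the SAP article, Internal validation names one object for the bootstrap: "The final predictive model will be internally validated using the bootstrap technique with 500 bootstrap samples". The selection step carried into the resamples is also named: "stepwise procedure will be repeated within each bootstrap sample". The stated outputs are that "a corrected c-index will be reported", that "Apparent and corrected calibration measures will be reported", and that the shrinkage factor is applied to the coefficients.

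Predictive performance lists two further indices: "Moreover, overall measures of performance, the Nagelkerke’s" R² "and the Brier score, will be provided", the Brier score being taken at 3 years. Neither is mentioned again under Internal validation.

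Statistical model and variable selection fixes the primary rule, "using a threshold of 0.10 for removal and 0.05 for re-admission of variables". Sensitivity analysis then repeats selection at other, unstated p-levels, with AIC (p ≤ 0.157) and with LASSO. Tenfold cross-validation is given there as the way to choose lambda, not as a way to estimate performance. The section closes with "The predictive performance of the models will be compared".

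**The concern.** Performance measured in the data that built a model is too favourable, and more so the more variables the selection rule lets in. The plan recognises this for the c-index and calibration of the final model. Two gaps remain.

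- The Brier score and R² of the final model would appear beside a corrected c-index without being corrected themselves.
- The comparison of selection rules has no stated basis. The only like-for-like figures that the text produces are apparent ones, which lean towards liberal rules. The other possibility, corrected for the final model and apparent for the rest, puts the primary rule at a disadvantage that has nothing to do with its quality.

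The Discussion acknowledges that there is no external validation, so internal validation carries the whole weight. The model is also meant to support risk groups for treatment decisions.

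**Working it through.** **1. The plan's own overfitting figure.** Inputs from Sample size: Cox-Snell R² 0.31, incidence rate 16%, mean follow-up 2.5 years. Target shrinkage S = 0.90 is assumed, in line with Internal validation, which treats values above 0.90 as small overfitting.
- Subjects per parameter = 1/[(S − 1) ln(1 − R²/S)] = 1/[−0.1 × ln(1 − 0.31/0.9)] = 23.68.
- Events per parameter = 23.68 × 0.16 × 2.5 = 9.47 (stated 9.5).
- Events among 400 at 40% = 160, and 160/9.5 = 16.8 (stated 17).

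The figures reproduce. The AIC level does too: P(χ² with 1 df > 2) = 0.157.

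**2. Candidates listed.** Twelve clinical and demographic predictors, five CSF measures, four hippocampal measures (two sides, two techniques), and MMSE, DFR, EEG, FDG-PET and APOE: 12 + 5 + 4 + 5 = 26, before extra parameters for multi-level variables. The check therefore uses 30 candidates (assumed) as well as the plan's 17.

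**3. Simulation at the planning values.** n = 400, c about 0.80, 40% or 27% events at 3 years. Assumed: 8 true predictors, pairwise correlation 0.3, administrative censoring only, backward elimination without re-entry, age and sex forced in. There were 150 data sets per setting, each model tested on 2,500 new subjects. Cells show apparent / new subjects.

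| Setting | Rule | c-index | Brier | Nagelkerke R² |
|---|---|---|---|---|
| 30 candidates, 40% | p 0.10 | 0.8121 / 0.7891 | 0.1386 / 0.1546 | 0.4428 / 0.3676 |
| | AIC | 0.8136 / 0.7885 | 0.1376 / 0.1552 | 0.4471 / 0.3639 |
| | p 0.50 | 0.8174 / 0.7858 | 0.1349 / 0.1575 | 0.4589 / 0.3486 |
| | LASSO | 0.8112 / 0.7926 | 0.1396 / 0.1518 | 0.4351 / 0.3866 |
| 30 candidates, 27% | p 0.10 | 0.8120 / 0.7818 | 0.1255 / 0.1435 | 0.3468 / 0.2526 |
| | AIC | 0.8149 / 0.7808 | 0.1240 / 0.1442 | 0.3536 / 0.2468 |
| | p 0.50 | 0.8211 / 0.7775 | 0.1209 / 0.1467 | 0.3683 / 0.2282 |
| | LASSO | 0.8108 / 0.7883 | 0.1267 / 0.1393 | 0.3380 / 0.2805 |
| 17 candidates, 40% | p 0.10 | 0.8080 / 0.7932 | 0.1411 / 0.1520 | 0.4344 / 0.3860 |
| | AIC | 0.8088 / 0.7935 | 0.1405 / 0.1519 | 0.4368 / 0.3864 |
| | p 0.50 | 0.8107 / 0.7929 | 0.1394 / 0.1524 | 0.4421 / 0.3834 |
| | LASSO | 0.8089 / 0.7945 | 0.1407 / 0.1509 | 0.4340 / 0.3934 |

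**4. Uncorrected indices of the primary-type rule (p 0.10).** Brier optimism: 0.1546 − 0.1386 = 0.016; 0.1435 − 0.1255 = 0.018; 0.1520 − 0.1411 = 0.011. R² optimism: 0.075, 0.094 and 0.048. A second simulation (377 studies, true c about 0.736, so below the planned 0.8) gave Brier 0.1620 apparent and 0.1805 true. Against a no-information value of 0.39 × 0.61 = 0.238, that is an apparent reduction of 32% and a real one of 24%.

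**5. Comparison on apparent c.** AIC minus p 0.10: apparent +0.0015, +0.0029, +0.0008; new subjects −0.0006, −0.0010, +0.0003. For p 0.50 minus p 0.10: apparent +0.0053, +0.0091, +0.0027; new subjects −0.0033, −0.0043, −0.0003.

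**6. Comparison of corrected with apparent c.** The optimism of the p 0.10 rule is 0.8121 − 0.7891 = 0.023, 0.8120 − 0.7818 = 0.030 and 0.8080 − 0.7932 = 0.015. The primary rule would trail by roughly this amount purely because it alone was corrected.

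**7. Does the remedy work?** With selection repeated in each resample (separate seed, 25 data sets, 30 resamples each; 30 candidates, 40% events), the gap in c between p 0.50 and p 0.05 fell from 0.0076 apparent to 0.0019 corrected. Most of the false advantage goes, but not all of it.

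**The case against.** A reader might infer that the plan prescribes a comparison on apparent performance, and that the most liberal rule will look best and be adopted. The documents do not support this. The Sensitivity analysis section never says apparent. It is a robustness check with no rule for switching models, and the nomogram and risk groups come from the final model.

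Nor is a large distortion shown.
- In the second simulation the mean apparent c was 0.769 for AIC and 0.767 for the primary 0.10/0.05 rule, with true c 0.736 for both.
- LASSO tied for the highest apparent mean (0.769), so a marked handicap for penalised models is not visible there.
- AIC beat a p < 0.05 rule on apparent c in 91% of studies and on true c in 46%, but that rule is not the primary one and the gaps are tiny.
- The larger contrasts in the table need p 0.50, a level the plan does not name. With 17 candidates, c in new subjects barely moves.

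It can also be said that an article condenses the full plan, and that the corrected c-index, calibration and shrinkage factor already reveal overfitting. Both points lower the weight of the concern without removing it. The text does more than stay silent: it states which model is bootstrapped, which procedure is repeated and which outputs are corrected. Followed as written, it yields an uncorrected Brier score and R², and no fair corrected comparison across rules.

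**Conclusion.** The point holds as a minor-to-moderate improvement. The firmer part is the final model's Brier score and R²: under the simulated assumptions the Brier score is too low by about 0.011 to 0.019, and R² too high by about 0.05 to 0.09. The comparison of selection rules lacks a fair basis. Its c-index distortion is about 0.001 to 0.003 for AIC against the primary rule if apparent values are used, more with looser p-levels or more candidates, and about 0.015 to 0.03 against the primary rule if corrected and apparent values are mixed. The choice of final model does not change.

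The sizes depend on assumed candidate numbers, effects and correlations. The two-stage selection and the re-entry step were not reproduced in the tabulated simulation. The optimism in all three indices appeared in every setting. So did the false apparent gain of p 0.50 over p 0.10, though with 17 candidates the loss in new subjects was close to nil.

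**What to change.** In Internal validation, add the 3-year Brier score and Nagelkerke R² to the measures corrected by bootstrap, and report apparent and corrected values side by side.

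In Sensitivity analysis, state the alternative p-levels. Run each alternative procedure in the same bootstrap resamples, repeating its selection every time and, for LASSO, the lambda search. Compare only the optimism-corrected c-index, calibration slope and 3-year Brier score.

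No new data are needed and the bootstrap is already planned. The cost is wording, computing time (chiefly the repeated LASSO tuning) and slightly less favourable reported figures. Since the bootstrap leaves a small residual lean towards liberal rules, differences of a few thousandths in corrected c should not be read as a ranking.
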